#### **Number of Investigators and Study Centres:**

Study centres will be located in the United Kingdom. Overall, it is estimated that approximately 18 centres and investigators will initially take part in the study.

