This Master Protocol outlines the overall structure of the study, including the population, inclusion and exclusion criteria, randomisation scheme, primary, secondary, and exploratory outcomes, study design, statistical methodology, and planned analyses that are common for all candidate agents to be tested. The Master Protocol is structured such that multiple candidate agents from different pharmaceutical companies can be evaluated simultaneously. The plan is to add candidate agents as they are identified, and to remove therapies once they have completed their evaluation, with the control group for a candidate agent including only patients randomised during the period in which the candidate agent group was randomised, with patients being randomised equally (ie, 1:1:1...) to the sub protocols with inclusion/exclusion criteria that they meet.

Sub-protocols will outline the scientific rationale, eligibility, treatment schema, and other specifics for each candidate agent. The sub-protocols may define adverse events of special interest (AESIs), and can include pharmacokinetic and/or pharmacodynamic assessments that are appropriate for the specific candidate agent (pharmacodynamic assessments may require

equivalent blood samples from controls). Additional patients will be recruited into the study each time a new sub-protocol (candidate agent) is added.

The study consists of 2 stages:

- **Stage 1** of the study (evaluation/pilot) will evaluate the candidate agents as an add-on to the standard of care (SoC) to assess preliminary safety and efficacy. A patient will be considered to be a responder if they show an improvement of at least 2 points (from randomisation) on a 9-point category ordinal scale, are discharged from hospital, or are considered fit for discharge (a score of 0, 1, or 2 on the ordinal scale), whichever comes first, by Day 29. The time to response will be analysed on Day 29 and used to evaluate if an agent should proceed to Stage 2 of the study. Stage 1 data will additionally be used to determine optimal study endpoints, and the number of patients to enrol into Stage 2 of the study.

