### 5.1 Inclusion Criteria

Patients are eligible to be included in the study only if all of the following criteria apply (as well as all criteria from the appropriate sub-protocol):

1. Adults ( $\geq 18$  years) with SARS-CoV-2 infection confirmed by laboratory tests and/or point of care tests.
2. A score of Grade 3 to 5 on the 9-point ordinal scale.
3. The patient, and their partner(s), agree to use medically-accepted double-barrier methods of contraception (eg, barrier methods, including male condom, female condom or diaphragm with spermicidal gel) during the study and for at least 6 weeks after termination of study therapy. A vasectomised partner would be considered an appropriate birth control method provided that the partner is the sole male sexual partner and the absence of sperm has been confirmed. If not, an additional method of contraception should be used.  
or  
The patient is a woman who is not of childbearing potential (as defined in Appendix 5)
4. Women who are lactating who agree not to breastfeed their child during the study and for at least 6 weeks after termination of study therapy (they may continue to express milk away from the child during this period, but this milk must be discarded).
5. Ability to provide informed consent signed by the study patient or legally authorised representative.

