### **6.3 Measures to Minimise Bias: Randomisation and Blinding**

No blinding will be used in this study.

The study will randomise participants on an ongoing basis to receive either one of the active candidate treatment arms as an add-on to SoC or to receive SoC alone. Randomisation will be stratified by study centre and baseline severity grade.

If additional arms (candidate treatments) are added to or dropped from the study, randomisation will proceed with an equal probability of assignment to each of the remaining arms, except for situations where a patient does not meet the inclusion/criteria for, and hence would be excluded from, one or more of the sub-protocols.

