#### Stage 2 (Confirmatory Stage)

This stage will focus on assessing potential candidate agents carried forward from Stage 1 with SoC. Further patients will be recruited into this stage of the study, with approximately

126 additional patients randomised to each arm. The set of patients in Stage 1 will not be included in the set of patients for Stage 2.

As in Stage 1, the time to a 2-point improvement on a 9-point category ordinal scale, discharge from hospital, or considered fit for discharge will be used to assess each candidate agent with SoC. Based on this endpoint, 126 patients will be needed per arm to observe an estimated 188 events across each candidate agent and SoC. This number of patients and events will provide 90% power to detect a hazard ratio of 1.6 for the occurrence of the event, when comparing each candidate agent with SoC. This calculation is based on a 1-sided test and a 2.5% significance level, and assumes the same response rates for the candidate agents and SoC as quoted for Stage 1.

### Stage 1 Leading into Stage 2

The analyses carried out at Stage 1, the pilot stage, will incorporate an assessment of which candidate agents to progress to Stage 2, the confirmatory stage. At the same time, the results observed at Stage 1 will facilitate decision making for Stage 2, allowing the selection of the primary analysis and endpoint, and the re-evaluation of sample size. If the proposed sample size for Stage 2 goes beyond 150 patients per arm based on the data observed at pilot stage, this must be ratified by the steering committee.

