| Primary     | 
Stage 1:
 
Time to 2-point improvement on the 9-point ordinal scale, live discharge, or fit for discharge (as analysed at Day 29), whichever comes first, will be compared with each treatment arm with standard of care (SoC) using log-rank test at the one-sided 0.1 alpha level. Patients in the Stage 1 Intention to Treat (ITT) set will be used.
 
Stage 2:
 
The time to 2-point improvement on the 9-point ordinal scale, live discharge, or fit for discharge (as analysed at Day 29), whichever comes first, analyses will be conducted between the selected treatments plus SoC and SoC alone. The primary endpoint could be re-determined based on Stage 1 results. Patients in the Stage 2 ITT set will be used for the following analyses:
 
The time to 2-point improvement on 9-point ordinal scale, live discharge, or fit for discharge at Day 29 will be conducted between each selected treatment group and control using the log-rank statistic, stratifying for study centre and baseline severity grade, and the p-value associated with the log-rank statistic will be compared at the 2-sided 0.05 alpha level. The hazard ratio between treatment arm and SoC will be estimated using Cox regression, including treatment, age category (age <70 years vs ≥70 years), baseline severity, age category and treatment interaction, baseline severity and treatment interaction as fixed effect, and study centre as random effect.
 |

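### Stage 2 is sized for an unstratified log-rank test, but Table 4 prescribes one stratified by centre and severity grade, which has less than 90% power if the hazard ratio of 1.6 holds within strata

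*Protocol*

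**What the plan says.** In Table 4 (Section 9.5.1), the Stage 2 primary comparison is made "using the log-rank statistic, stratifying for study centre and baseline severity grade". The same cell estimates the hazard ratio by Cox regression with study centre as a random effect. The Stage 1 entry names a log-rank test without strata, and so does Section 9.2 for Stage 2.

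Section 9.3 gives the Stage 2 size: "126 patients will be needed per arm to observe an estimated 188 events across each candidate agent and SoC". It adds: "This number of patients and events will provide 90% power to detect a hazard ratio of 1.6". The calculation uses one-sided 2.5% and Day 29 response rates of 85.5% against 70%. The text above Table 2 says only that the sizes come from a log-rank test; no strata and no allowance for them are mentioned.

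The number of cells follows from three other places. The Synopsis and Section 4.1 expect that "approximately 18 centres and investigators will initially take part in the study". Section 5.1 admits "A score of Grade 3 to 5 on the 9-point ordinal scale". Section 6.3 says: "Randomisation will be stratified by study centre and baseline severity grade". No block size is given.

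**The concern.** The protocol sizes one test and prescribes another. A stratified log-rank test compares patients only within a cell. Once a cell has patients at risk from one arm only, its later events contribute nothing. With fewer than five patients per cell and response rates of 70–85.5%, this happens early and often. Stratifying by three grades costs almost nothing; crossing grade with every centre is what makes the cells sparse.

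At stake is the type II error of the confirmatory stage. An effective agent could be missed more often than the planned 10%, for a reason that one phrase can remove.

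**Working it through.** **Inputs from the protocol.** 126 per arm, 188 events, 90% power, one-sided 2.5%, rates 70% and 85.5% (Section 9.3); about 18 centres (Section 4.1); Grades 3, 4 and 5 (Section 5.1); equal allocation (Section 4.1).

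**1. The stated figure.** Under proportional hazards the rates imply HR = ln(0.145)/ln(0.30) = 1.604. Schoenfeld events: 4 × (1.96 + 1.2816)² / (ln 1.604)² = 188.3, against 188 stated. Power at 188 events is 89.95% at HR 1.604 and 89.7% at HR 1.6. Freedman's formula gives 196 events, and 196/(0.70 + 0.855) = 126 per arm. Both formulas are unstratified, so the stated figure is right for an unstratified test.

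**2. Cells.** 18 × 3 = 54; 2 × 126 = 252; 252/54 = 4.7 patients per cell.

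**3. Power of the prescribed test at HR 1.604 in every cell.** Assumed for the simulation: exponential times, daily assessment, censoring after 28 days, no dropout, no prognostic effect of centre or grade. There were 2,000 trials per row (800 for 10 centres). Monte Carlo standard error is about 0.8 points at 83%: √(0.83 × 0.17/2000).

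| Scenario | Centre × grade | Grade only | Unstratified | Information (same order) |
|---|---|---|---|---|
| 18 equal centres, blocks of 4 in cells | 83.6% | 91.0% | 91.0% | 35.8 / 44.7 / 45.0 |
| 18 skewed centres, blocks of 4 | 83.3% | 90.6% | 91.0% | 36.0 / 44.6 / 45.0 |
| 18 centres, grade mix 15/60/25, blocks of 4 | 82.7% | 91.2% | 91.4% | 36.1 / 44.7 / 45.1 |
| 18 equal centres, arms not balanced in cells | 76.4% | 91.2% | 91.9% | 30.1 / 44.4 / 45.0 |
| 18 skewed centres, arms not balanced | 78.4% | 91.4% | 91.4% | 31.2 / 44.5 / 45.1 |
| 10 centres, blocks of 4 | 87.2% | 89.9% | 89.8% | 40.2 / 44.8 / 45.2 |

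The unstratified test sits slightly above 90% because 252 patients yield about 196 events. The information loss is 1 − 35.8/45.0 = 20% with blocks and 1 − 30.1/45.0 = 33% without balance. Separate runs on the same assumptions gave 81–85% with blocks, 74–78% without balance, and 89% at 10 centres.

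The unbalanced case matters because no block size is stated, and because eligibility that differs by sub-protocol need not leave each pair of arms balanced in each cell.

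**4. Check by formula.** Power ≈ Φ(ln(1.604) × √V − 1.96), with ln(1.604) = 0.4725:
- V = 45.0: Φ(3.170 − 1.96) = 89%
- V = 35.8: Φ(2.827 − 1.96) = 81%
- V = 30.1: Φ(2.592 − 1.96) = 74%

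The levels are two to three points below the simulation and the drop is about the same.

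**5. Prognostic strata, overall rates held at 70% and 85.5%.** The strengths below are assumptions, since the protocol gives none: 18 centres, blocks of 4, 1,200 trials per row.

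| Centre SD; relative hazards by grade | Within-stratum HR | Centre × grade | Grade only | Unstratified |
|---|---|---|---|---|
| 0.3; 1.5/1/0.6 | 1.74 | 89.8% | 95.5% | 93.3% |
| 0.3; 2/1/0.4 | 1.94 | 97.3% | 98.8% | 96.3% |
| 0.5; 2/1/0.4 | 2.00 | 98.9% | 99.8% | 97.8% |

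**6. Size needed if all 54 cells stay** (HR 1.604, homogeneous strata, blocks of 4). 290 patients in total give 87.3% and 310 give 90.8%, so about 300–310, or 150–155 per arm.

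**7. Validity.** With no treatment effect, the prescribed test rejected in 1.9% of 1,200 trials, against a nominal 2.5%.

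**The case against.** A reader might infer that the confirmatory test simply does not have 90% power. The documents do not support that. The hazard ratio of 1.6 follows from the overall Day 29 rates, so it is the within-stratum ratio only if grade and centre do not predict response. Under Section 8.1.1 a Grade 3 patient responds on reaching score 2, one step away, while a Grade 5 patient needs two steps, so some prognostic effect of grade is plausible. If so, and if the overall rates hold, the within-stratum ratio is above 1.6 and the prescribed test can reach the target (step 5). This part stands. What remains is that Section 9.3 claims its power at a ratio of 1.6, not at 1.74 or more, and that grade-only stratification was more powerful in these scenarios too.

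A reader might also add prognostic effects, hold the within-stratum ratio at 1.604, and blame the whole shortfall on the strata. In such runs the overall rates are no longer those of the protocol, and the unstratified test also falls to about 80%, so much of that loss is not due to stratification.

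Three further points stand in part. Eighteen is an approximate, initial count for the platform, and fewer active centres shrink the loss. A pooling rule for small centres may be in the statistical analysis plan, so its absence here is no finding. Sections 9.3 and 9.6 re-evaluate the sample size after Stage 1, but an unstratified formula used again would repeat the mismatch.

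Finally, analysing by the randomisation factors is conventional, and the test is valid. The issue is efficiency against a stated power, not type I error.

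**Conclusion.** The mismatch between the sizing and the prescribed test is established from the text. Its size is conditional. If the hazard ratio of 1.6 holds within strata and about 18 centres contribute, power is roughly 81–85% with block balance and about 75–78% without it, so type II error is about 15–25% instead of 10%. At 10 centres power is about 87–89%. With strongly prognostic strata and overall rates of 70% and 85.5%, power can be about 90% or more. The protocol does not give the centre sizes, grade mix, block size or prognostic strength needed to choose among these, so no single figure such as 82% should be quoted. The point is worth correcting before Stage 2 begins; it does not make the test invalid.

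**What to change.** In Table 4, stratify the Stage 2 primary log-rank test by baseline severity grade only (three strata), and keep study centre as the random effect already specified in the Cox model. Under the step 3 assumptions this keeps about 90% power at 126 per arm. It changes one phrase. The small downside is that the test no longer adjusts for centre, a randomisation factor; a centre-stratified test can be kept as a sensitivity analysis.

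If centre stays as a stratum, restate the Stage 2 power in Section 9.3 for the stratified test, as a range with its assumptions on number of centres, block size and grade mix. Use that same test in the re-evaluation after Stage 1. Under the step 6 assumptions, regaining 90% takes about 150–155 per arm, 24–29 more than 126. That is at or just past the 150 per arm beyond which Section 9.3 requires steering committee ratification.

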### **9.2 Statistical Hypotheses**

The primary hypothesis at Stage 1 is time to response (2-point improvement in the 9-point ordinal scale, live discharge from hospital, or considered fit for discharge, as analysed at Day 29) of the candidate arm is shorter than the SoC.

The primary hypothesis at Stage 2 is time to response (as analysed at Day 29) of the candidate arm is shorter than the SoC.

As the events are 2-point improvement in 9-point ordinal scale, live discharge, or considered fit for discharge, a hazard ratio (HR) larger than 1 is favourable to the test treatment, with the HR comparing the test treatment with the control.

$$H_0: HR \leq 1 \text{ vs } H_A: HR > 1$$

No multiplicity adjustment will be made for the fact that each candidate arm will be compared with the control arm (SoC). In Stage 2, each comparison will be tested at the Type I error rate=0.05 (1-sided alpha=0.025) using a log-rank test; HR will be estimated based on the Cox regression model.

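### The Stage 2 Cox model in Table 4 contains treatment interactions, so as written it defines up to six subgroup hazard ratios and no single overall one

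*Protocol*

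**What the plan says.** Protocol Section 9.2 sets out one HR per comparison. It says that "a hazard ratio (HR) larger than 1 is favourable to the test treatment", tests the null that the HR is at most 1 with a log-rank test, and adds that "HR will be estimated based on the Cox regression model". Section 9.3 sizes Stage 2 on the same single quantity: "126 patients will be needed per arm to observe an estimated 188 events across each candidate agent and SoC", and "This number of patients and events will provide 90% power to detect a hazard ratio of 1.6 for the occurrence of the event".

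Table 4 (Primary, Stage 2) gives the detail. The test is one overall log-rank comparison per selected agent: "stratifying for study centre and baseline severity grade, and the p-value associated with the log-rank statistic will be compared at the 2-sided 0.05 alpha level". Estimation is specified separately: "The hazard ratio between treatment arm and SoC will be estimated using Cox regression, including treatment, age category", followed by baseline severity and then "age category and treatment interaction, baseline severity and treatment interaction as fixed effect, and study centre as random effect".

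No other part of the protocol states how the covariates are coded, how the interaction terms are averaged, or that a model without them supplies the headline HR.

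**The concern.** Once treatment interacts with age category and with baseline severity, the model no longer has one treatment effect. The log HR depends on the patient's age group and grade, and the coefficient labelled treatment means whatever the coding makes it mean. Under the usual reference coding it describes a single age-by-severity cell. That is neither the overall difference that the stratified log-rank test addresses nor the HR of 1.6 behind the sample size.

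What is at stake is the effect estimate and confidence interval reported for the confirmatory stage. They could describe a minority of patients, with an interval wide enough to include 1 in a trial whose primary test succeeded.

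**Working it through.** **1. The plan's own figure.** Inputs from Section 9.3: response by Day 29 of 70% (SoC) and 85.5% (candidate), 1-sided 2.5% level, 90% power.
- Implied HR = ln(1 − 0.855) / ln(1 − 0.70) = 1.931 / 1.204 = 1.604.
- Schoenfeld events = 4(1.960 + 1.282)² / (ln HR)². This gives 191 at HR 1.6 and 189 at HR 1.604 after rounding up (188.3 before), against 188 stated.
- Power with 188 events at HR 1.6 is 0.897. The plan's figure is reproduced, for one overall HR.

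**2. What the Table 4 model estimates.** Section 5.1 admits Grades 3 to 5, and Table 4 splits age at 70. With severity as a three-level factor,

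log HR = b(treatment) + b(age)·[≥70] + b(grade),

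which gives 2 × 3 = 6 cell HRs. Under reference coding, exp b(treatment) is the HR in the reference cell only.

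**3. Precision of the overall HR.** Without interactions, 1:1 allocation and 188 events give SE(log HR) ≈ √(4/188) = 0.146. At HR 1.6 the 95% interval is 1.6 × exp(±1.96 × 0.146) = 1.20 to 2.13.

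**4. Precision of the reference-cell coefficient.** Let p be the share aged ≥70 and p0 the share in the reference grade. If the two are independent and events are spread in proportion to patients, the variance is multiplied by 1 + p/(1 − p) + (1/p0 − 1). The documents give neither p nor p0, so the values below are assumptions.
- p = 0.4, p0 = 0.33: 1 + 0.667 + 2.03 = 3.70, so SE × 1.92 = 0.28.
- p = 0.4, p0 = 0.20: 1 + 0.667 + 4 = 5.67, so SE × 2.38 = 0.35.

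**5. Simulation check.** Settings: 126 per arm, true HR 1.6 in every cell, exponential times, 28 days of follow-up, assumed prognostic effects of age and grade, no centre effect, 60 replicates per mix (percentages carry a Monte Carlo error of about 3 to 6 points).

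| Assumed mix: ≥70; Grades 3/4/5 | SE by formula, reference coding | SE simulated, reference coding | SE, no interactions | SE, interactions mean-centred | Lower 95% limit above 1: reference / none / centred |
|---|---|---|---|---|---|
| 30%; 33/34/33 | 0.27 | 0.258 | 0.149 | 0.151 | 53% / 80% / 82% |
| 40%; 25/50/25 | 0.32 | 0.305 | 0.151 | 0.153 | 35% / 93% / 90% |
| 50%; 15/60/25 | 0.40 | 0.391 | 0.152 | 0.155 | 18% / 85% / 87% |

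A further run with 20% of patients in Grade 3 gave 0.34. The working range is 0.26 to 0.34, and the most uneven mix reached 0.39.

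**6. What this does to the interval at HR 1.6.**
- SE 0.26: 1.6 × exp(±0.510) = 0.96 to 2.66; z = 0.470/0.26 = 1.81.
- SE 0.34: 1.6 × exp(±0.666) = 0.82 to 3.12; z = 0.470/0.34 = 1.38.
- The overall comparison has z = 0.470/0.146 = 3.22.

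An observed HR of exactly 1.6 would therefore pass the primary test comfortably, while the reference-cell interval includes 1.

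**7. If the effect differs between cells.** Assume a reference-cell HR of 1.1, multiplied by 1.4 at ≥70 years, 1.3 in Grade 4 and 1.6 in Grade 5, with the 40%; 25/50/25 mix. The patient-weighted mean log HR is ln 1.1 + 0.4 ln 1.4 + 0.5 ln 1.3 + 0.25 ln 1.6 = 0.479, an HR of 1.61. Median estimates were 1.62 without interactions, 1.65 mean-centred and 1.13 for the reference-coded coefficient. In this case the point estimate moves as well as the width.

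**The case against.** The strongest reply is that Table 4 does not say the reported HR will be the treatment coefficient, and does not set reference coding. The same model with mean-centred covariates, or with an averaged contrast, returns an overall HR with an SE of 0.151 to 0.155, close to the main-effects model. Section 9.5 defers detail to an SAP with addenda, and coding and contrasts are normal SAP content. Sections 9.3 and 9.6 also leave the Stage 2 analysis open to re-evaluation after Stage 1.

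Much of this stands, and it rules out three stronger readings.
- A reader might infer that the planned HR simply is the effect in one reference subgroup. That holds only under reference coding, which the protocol does not prescribe.
- A reader might infer that Stage 2 loses power. It does not: the p-value comes from the log-rank test, and no rule depends on the Cox interval excluding 1. The percentages in the last column of the table are not the power of any planned test.
- A reader might infer that severity will enter as a number, so that the coefficient refers to Grade 0. The protocol uses severity grade as a stratification factor and gives no support for that.

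What does not stand is treating this as detail left to the SAP. The protocol itself places the interactions in the sentence that defines the HR. An SAP that follows Table 4 must add a contrast the protocol does not mention, and one that drops the interactions departs from the protocol.

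Nor does removing them guarantee agreement with the test, which stratifies by centre and severity and ignores age. In a check with 18 centres by 3 grades as strata (150 replicates per scenario), interval and test disagreed in 13–19% of trials without interactions, 15–18% with mean-centring and 41–49% with reference coding.

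**Conclusion.** The point holds for the reported Stage 2 effect estimate and its interval, and for nothing else. As written, Table 4 yields up to six subgroup HRs and does not define the single HR that Section 9.2 tests and Section 9.3 sizes on. If the treatment coefficient is read off under reference coding, its SE is about 1.7 to 2.3 times as large (0.26 to 0.34 against 0.15). The interval at HR 1.6 then includes 1, and under differing effects the estimate itself can move far from the overall HR.

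These sizes rest on assumed age and severity mixes, assumed prognostic effects and no centre effect. The direction was the same in every mix tried. Mean-centring or an averaged contrast largely removes the problem, but the protocol specifies neither. The log-rank test, its type I error and power, the 188 events and the 126 patients per arm are unaffected.

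**What to change.** In Table 4, take the headline Stage 2 HR and 95% interval from a Cox model without treatment interactions. It can contain treatment, baseline severity (as stratum or fixed effect), age category and centre as random effect, or it can be stratified exactly as the log-rank test is, which brings estimate and test closest together. Fit the treatment-by-age and treatment-by-severity interactions in separate supportive models and report the subgroup HRs from those.

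If the sponsor prefers to keep the interactions in the main model, the alternative is to state in advance the weighted contrast that defines the overall HR.

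The cost is one sentence in Table 4 and matching SAP text, with no new patients or data. It should be settled before any Stage 2 analysis.
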